## Abstract

**Background:**

According to the first law of thermodynamics, energy cannot be created or destroyed in an isolated system. Water has a characteristically high heat capacity, indicating that the temperature of ingested fluids and meals could contribute to energy homeostasis. Citing the underlying molecular mechanisms, we present a novel hypothesis that states that the temperature of one’s food and drink contributes to energy balance and plays a role in the development of obesity. We provide strong associations with certain molecular mechanisms that are activated by heat and correlate them with obesity and a hypothetical trial that could test this hypothesis. We conclude that if meal or drink temperature proves to contribute to energy homeostasis, then depending on its contribution and scale, future clinical trials should attempt to adjust this effect when analyzing data. In addition, previous research and established relationships of disease states with dietary patterns, energy intake, and food component intakes should be revisited. We understand the common assumption that thermal energy in food is absorbed by the body during digestion and dissipated as heat into the environment, not contributing to the energy balance. We challenge this assumption herein, including a proposed study design that would test our hypothesis.

**Objective:**

This paper hypothesizes that the temperature of ingested foods or fluids influences energy homeostasis through the expression of heat shock proteins (HSPs), especially HSP-70 and HSP-90, which are expressed to a greater extent in obesity and are known to cause deficits in glucose metabolism.

**Methods:**

We provide preliminary evidence supporting our hypothesis that greater dietary temperatures disproportionally induce activation of both intracellular and extracellular HSPs and that these HSPs influence energy balance and contribute to obesity.

**Results:**

This trial protocol has not been initiated and funding has not been sought at the time of this publication.

**Conclusions:**

To date, no clinical trials are available regarding the potential effects of meal and fluid temperature on weight status or its confounding effects in data analysis. A potential mechanism is proposed as a basis by which higher temperatures of foods and beverages might influence energy balance via HSP expression. On the basis of the evidence supporting our hypothesis, we propose a clinical trial that will further elucidate these mechanisms.

**International Registered Report Identifier (IRRID):**

PRR1-10.2196/42846

## Introduction

### Background

The first law of thermodynamics, also known as the law of conservation of energy, states that energy can neither be created nor destroyed in an isolated system [1]. The human body has its own mechanisms to adapt to changing temperatures; however, it is possible that higher or lower temperatures of food and beverages (referred to as dietary temperature) impose some implications on the energy demands of the body. On the basis of diet composition, chewing habits, and the amount of fluid (and its corresponding temperature) ingested, the human body is exposed to a wide range of temperatures [2,3]. This exposure affects the entire gastrointestinal tract, being greatest at the mouth, followed by the esophagus and stomach, with the latter exposed for a greater time [4-7]. Indeed, there have been several studies relating dietary temperature to gastric function [6], frequency of gastric myoelectrical activity [7], gastric emptying time, gastrin release, gastric acid secretion [8], esophageal cancer [9,10], and intraluminal upper gastrointestinal temperature and motility [5]. Although when it comes to energy metabolism, it has been assumed that higher dietary temperatures are dissipated during digestion and do not contribute to energy balance.

One of the most immediate responses of body cells to higher temperatures is the induction and increased synthesis of heat shock proteins (HSPs), especially HSP-70 [11,12] and HSP-90 [13,14]. HSP-70 [15] and HSP-90 [16] possess N-terminal adenosine triphosphatase fragments at their ends and tightly regulate adenosine triphosphate (ATP) activity and ATP hydrolysis [13,17-19], providing the heat energy to drive the adenosine diphosphate to ATP conversion. Indeed, cells exposed to higher temperatures increase HSP activity [11-14], and the time profile of peripheral blood mononuclear leukocytes HSP-70 response to in vitro heat shock is temperature dependent [11,20]. For instance, under in vitro hyperthermic conditions (40-41 °C), the time course was characterized by a sharp rise in HSP-70 concentration immediately after heat shock treatment (*P*<.05 for 40 °C at 0 hours), followed by a steady and progressive decline over time [11].

We have already shown that HSPs can extract energy from the environment (here, dietary temperatures), thereby contributing to the energy balance. The mathematical calculations are beyond the scope of this paper, and interested readers may read our previous paper [21]. The summary is graphically illustrated in Figure 1.

Importantly, obesity has been linked to HSP expression, specifically for HSP antibodies (HSP-27 [22], HSP-72 [23], HSP-60, HSP-65, and HSP-70 [24,25]). The table in the Multimedia Appendix 1 [22,24-26] lists the studies investigating the relationship between anti-HSP antibodies and indexes of body mass and body composition. Specifically, serum HSP-27, HSP-60, HSP-65, HSP-70, and HSP-72 antibody levels are significantly increased in people with obesity compared to people with a normal weight [22-26]. Furthermore, in the diet-induced obese mouse model of insulin resistance, HSP-90 inhibitors activate the heat shock factor 1 stress response pathway and improve glucose regulation [27]. A similar experiment on diet-induced obese mice supports this hypothesis in which HSP-90β knockdown reverses insulin resistance and improves glucose tolerance [28].

**Figure 1 figure1:**
[figure not shown]
Hypothetic mechanism by which hot meals or drinks may contribute to energy balance. ADP: adenosine diphosphate; ATP: adenosine triphosphate; ATPase: adenosine triphosphatase.

### Evidence Supporting Our Hypothesis

#### Intracellular Versus Extracellular HSPs

HSPs help to maintain cellular homeostasis through a mechanism called thermotolerance. Cells exposed to mild stress induce HSPs, which later protect them against subsequent stress. In cells exposed to severe stress, HSPs promote apoptosis. HSPs meanwhile exist in extracellular fluids and contribute to immunomodulation [29]. It is noteworthy that the intracellular HSP function may be different from that of extracellular HSPs, as the latter appears to manifest a function different from the well-known chaperone role [29]. For instance, intracellular HSP-70 exerts a profound anti-inflammatory effect, whereas extracellular HSP-70 activates proinflammatory pathways [30]. In the case of obesity, both intracellular [31] and extracellular [32] HSP-70 levels are significantly greater in participants with obesity than in lean controls. It has been proposed that the ratio of extracellular medium HSP-70 to intracellular HSP-70 contents may be a determining factor to trigger a chronic proinflammatory status, which leads to insulin resistance and the development of type 2 diabetes mellitus (T2DM) [30].

#### Weight Regain and HSPs

In the only published randomized controlled trial (RCT) linking weight regain to HSPs, Roumans et al [33] explored the expression of stress proteins during weight loss and weight maintenance concerning weight regain. They compared the in vivo findings with the results from in vitro cultured human Simpson-Golabi-Behmel syndrome (SGBS) adipocytes. In total, 18 healthy participants participated in an 8-week dietary program with a 10-month follow-up period. They categorized the participants as weight maintainers or weight regainers based on their weight changes during the intervention. Abdominal subcutaneous adipose tissue biopsies were conducted before and after the diet and after the follow-up. In vitro–differentiated SGBS adipocytes were starved for 96 hours with low (0.55 mmol/L) glucose. Weight regainers showed increased expressions of calnexin, β-actin, HSP-27, HSP-60, and HSP-70. Changes in HSP-27 and HSP-70 and β-actin levels were linked to HSP-60, a novel key factor in weight regain after weight loss. SGBS adipocytes manifested increased concentrations of β-actin and HSP-60 after 96 hours of glucose restriction [33]. In another RCT, 20 young overweight men without metabolic syndrome participated in a 3-week residential program on a low-fat diet and moderate aerobic exercise. After 3 weeks of the diet program, significant reductions in BMI, serum lipids and lipid ratios, and oxidative markers were recorded (*P*<.05), along with the reduced expression of HSP-90 and HSP-27 [34].

There is ample literature on the effects of heat stress on fat deposition [35], insulin sensitivity [36], and the facilitating role of HSPs in adiposity [37-39]. The most direct evidence supporting our hypothesis comes from studies conducted on pigs. Exposure to low or high ambient temperatures directly impacts heat production and energy balance in pigs [40]. Heat stress causes enhanced adiposity [41] and growth performance through reduced energy and nitrogen use [42]. However, it is noteworthy that novel observations challenge this long-held traditional dogma, linking reduced productive output during heat stress to decreased nutrient intake. It is now clear that the heat stress response profoundly changes postabsorptive carbohydrate, lipid, and protein metabolism independently of decreased feed intake through harmonized alterations in fuel supply and use by various tissues [43]. One might argue whether heat stress in pigs is relevant to the effects of food temperature on energy metabolism in humans, especially when there is no direct evidence to show that ingesting hot food raises body temperature to such an extent. In addition, it may be argued that the association of HSPs with obesity does not automatically infer causation, and it is well known that these systems respond to metabolic stress. Therefore, to test this hypothesis, we prepared a short proposal to conduct a clinical trial, as described in the *Methods* section.

Altogether, these trials might provide preliminary evidence that HSPs contribute to obesity and weight regain. There is evidence that other HSPs, that is, HSP-A12A, regulate adipocyte differentiation and diet-induced obesity through positive feedback regulation with PPARγ (peroxisome proliferator-activated receptor gamma) [44].

To explore the mechanism of the effects of heat stress on porcine adipocytes, Qu et al [35] used an in vitro adipocyte differentiation model to determine the cellular responses that occur during adipocyte differentiation in pigs. Stromovascular cells (preadipocytes) were differentiated for 9 days at a normal (37 °C) or heat stress (41.5 °C) temperature under 5% CO_2_. They measured the expression of a long list of heat stress genes, such as HSP-27, HSP-60, HSP-70, and HSP-90, as well as cellular triglyceride and ATP concentration. Expectedly, heat stress significantly enhanced the expression of HSP genes but surprisingly had no effect on the level of PPARγ, although C/EBPα was significantly induced. Heat stress leads to the enhanced expression of genes involved in fatty acid uptake and cellular triglyceride synthesis. With the progression of differentiation, the total cellular ATP significantly decreased. However, cells under heat stress had significantly greater cellular ATP than those under control temperature. They concluded that heat stress promoted increased adipocyte triglyceride storage, possibly through the upregulation of genes involved in fatty acid uptake and triglyceride synthesis [35]. It was later determined that the induction of phosphoenolpyruvate carboxykinase expression in adipose tissue by heat stress indicates that increased glyceroneogenesis might also be involved in increased fat storage in pigs under heat stress [38].

Although exposure to a higher dietary temperature is a different form of exposure to higher environmental heat in animals, these animal studies [35,40-42] have invaluable lessons that can be translated into a clinical trial. The temperature range of heat stress applied usually lies between 37 °C and 41.5 °C for in vitro studies [35], which can theoretically simulate physiological responses during eating and drinking of hot meals and drinks, and ranges between 12 °C and 29 °C for exposure to ambient temperature studies [40], which is an acceptable temperature difference range (Δ) to study higher or lower dietary temperatures in humans.

Participants with obesity showed increased expression of HSP-60, HSP-72, HSP-90, and GRP-94 levels, specifically influencing BMI and percent body fat [45], whereas insulin resistance resulted in a decrease in intracellular HSP-70 levels. It also appears that weight loss can reduce HSP activation, as demonstrated in a recent trial where acupuncture in combination with dietary restriction was effective in reducing all immunologic factors (anti-HSP antibodies including anti–HSP-27, anti–HSP-60, anti–HSP-65, and anti–HSP-70) and weight loss [46]. Altogether, these findings indirectly support the hypothesis that a network composed of different HSPs (mainly HSP-70 and HSP-90, but including other HSPs, possibly via modulation of insulin sensitivity or resistance) may alter energy balance and contribute to weight gain and loss, which may have important implications in obesity treatment and prevention.

#### Thermic Response

Although the higher temperature of ingested meals and fluids may have some overlap with specific dynamic action (SDA), it should be emphasized that these are 2 different concepts; meal or fluid temperature is a subset of SDA, whereas SDA, or thermic response, is a physiological phenomenon, which comprises the energy expended on all activities of the body after the ingestion of a meal and leads to a rapid postprandial increase in the metabolic rate. SDA is influenced by the size, type, composition, and temperature of the meal as well as body size, body composition, and multiple environmental factors (such as gas concentration and ambient temperature). In humans, a commonly used estimate of the thermic effect is approximately 10% of the caloric intake; however, the average maximum increase in metabolic rate originating from digestion could reach 25% [47].

However, there is indirect evidence that states that meal temperature might influence energy balance, which is not accounted for by SDA. Meal temperature is one of the determining factors of gastric emptying and absorption of food compositions such as carbohydrates in the duodenum [48], which consequently affects heart rate [8] and thereby metabolic needs. In endotherms, including humans, if meals and fluids are ingested at a temperature lower than the core body temperature, extra heat should be generated to elevate the meal temperature to the body temperature. Thus, the cost of food warming is indicated by the SDA response [47]. The contribution of food warming to SDA should vary as a function of meal temperature and mass. In other words, more energy is expended to warm a large, cold meal compared with a smaller, warmer meal [49]. It might be conjectured that the reverse may hold true for warmer meals and fluids and thereby contribute to energy expenditure and thus energy balance.

The results of direct or indirect calorimetry studies can be criticized; these studies are usually short term and do not account for the influence of between-individual differences in dietary temperatures, neither on the day of calorimetry measurements nor the day before. It might be a good practice to advocate the measurement or control of meal temperature during the day of measurement and at least 1 week before indirect calorimetry. A careful appraisal of the methodology of most laboratory studies shows that, at best, participants are asked to refrain from caffeine and alcohol intake and any vigorous physical activity 1 day before the calorimetry study or a standard diet is prescribed [50-54]. It can also be argued that heat acclimation may partially promote thermoregulatory adaptations in people who consume hot foods and fluids. This might be true; however, this has not been experimentally tested. In addition, there might be an interaction between dietary temperature and some ingredients of food composition (for instance, capsinoids) or some dietary behaviors (such as the frequency of consuming ingredients like capsinoids) that might circumvent thermoregulatory pathways.

In a recent meta-analysis, increases in HSP-70 protein expression after heat acclimation were shown to be moderated by the number of heat acclimation days [12]. In other words, there is a strong possibility that between-individual differences in eating behaviors in terms of the temperature of foods and drinks they consume may influence HSP-70 expression and, if HSP-70 expression contributes to energy balance, then this will confound matching protocols in clinical trials, such as treatment-matching, subject-matching, and data-matching protocols.

### Evidence From the Effect of Dietary Temperature on Food and Liquid Intake

Although the current hypothesis is centered on the influence of dietary temperature on HSPs to cause changes in metabolic processes that favor energy storage, a potential confounding effect that may exist is the effect dietary temperature may have on eating behaviors. In an experiment conducted on rats, no interaction was reported between nurture temperature and meal temperature. The food temperature per se had no significant effect on food intake [55]. In contrast, food temperature had an impact on food intake in patients who were hospitalized. The percentage of hospitalized patients who rated the meal temperature as good was higher for those served with isothermal trolleys than those who were not. The amount of food consumed by patients served with isothermal trolleys was significantly greater than that consumed by patients served without the trolleys [56]. Similar results have been obtained in another hospital setting [57]. Furthermore, serving temperature may affect expected satiety and complementary food purchases. Consumers are more likely to choose complementary food items when they consume or intend to consume a food or beverage served cold rather than hot [58], and warm temperature attenuates the preference for savory meals [59]. The dietary temperature may additionally influence executive function and processes associated with obesity, whereas lower executive function acts as a risk factor for increases in specific eating behaviors that play a role in the development of weight management problems [60,61]. Therefore, the dietary temperature may have a complex interaction with total energy consumption, which deserves to be clinically investigated under controlled conditions.

The aforementioned literature justifies the need to conduct a well-controlled clinical trial to test whether higher dietary temperatures interfere with body and cellular energetic states and, thus, influence or confound the results of clinical trials that aim to compare or evaluate dietary interventions.

## Methods

### Overview

To the best of our knowledge, no studies are available regarding the possible contribution of dietary temperatures to the HSP response. We provide preliminary evidence supporting our hypothesis that higher dietary temperatures disproportionally induce activation of both intracellular and extracellular HSPs and that these HSPs influence energy balance and obesity. In this paper, we outline a protocol to test these hypotheses and elucidate the potential roles dietary temperature plays in obesity development.

### A Proposal to Conduct an RCT

A 4-arm randomized design investigating diets served at different temperatures in 5 °C increments (with core body temperature as a reference) in healthy adults would be the first step to elucidate the potential mechanism linking higher meal temperature with energy contribution. The same protocol can be replicated in patients who are overweight and obese or in people with T2DM. In addition, a crossover design can be performed with necessary modifications.

### Participants: Inclusion and Exclusion Criteria

The participants will include 80 healthy (BMI 25-35 kg/m^2^) men and women aged 19-65 years. Entry criteria will include people who are not currently dieting to lose weight and have had no weight loss or gain >2 kg over the past 3 months; not taking any medications (including antifever) that affect energy expenditure or eating; not using tobacco; not pregnant or lactating or planning to become pregnant in the next 12 months; and have no limitations to eating specific foods or to swallowing (eat and drink) a normally estimated range of meal temperatures (37-52 °C). The participants must not have major health problems; known cardiovascular (cardiac, peripheral vascular, and cerebrovascular), pulmonary (chronic obstructive pulmonary disease, interstitial lung disease, and cystic fibrosis), or metabolic (diabetes, thyroid disorders, and renal or liver disease) disease; and severe fever.

### Procedures

The day before the experimental session, the participants will be instructed to avoid alcohol, caffeine, and strenuous exercise and to drink plenty of water for 24 hours. On the day of the experimental session, the participants will be asked to arrive at the laboratory adequately rested and will be provided with boluses of soups (each 100 ml) with a predefined temperature to be taken once (to overcome the problem of temperature dissipation).

The energy content of bolus diets (including the thermoneutral diet and temperature-graded bolus diets) will be matched to each of the participant’s objectively calculated energy demands [62] and will be provided in the following manner: 20% energy for breakfast, 50% for lunch, and 30% for dinner. This procedure will facilitate the administration of boluses with graded temperatures (eg, +5 °C increments) with a fair precision from 37 °C to 52 °C, which is both ethical and within the optimal drinking temperature of 57.8 °C and <85 °C for the maximum temperature used to serve hot drinks such as coffee [63].

After assuring sufficient hydration (urine-specific gravity <1.025) [64], the participants will be instrumented in a thermoneutral room (approximately 25 °C) and then will be entered into a whole-body calorimeter regulated to 35 °C with approximately 20% relative humidity, where they will rest in an upright seated position for a 30-minute habituation period while steady-state measurements will be obtained.

The dietary temperature will be measured using a noncontact thermometer. All drinks and a standardized diet will be served at room temperature to maximize gastric emptying and fluid uptake while minimizing diuresis. It is expected that by using this metered intake to control for intake pacing, ingestion will be completed between 3 minutes and 5 minutes and will control for heat dissipation of foods and fluids as well. To avoid thermal injury while providing a satisfactory sensation to the participants, the optimum temperature for serving hot fluids and meals will be observed [63].

The drinks and meals will be consumed at a speed that is as rapid as the participants can comfortably manage, which is described elsewhere in detail (mean 11 seconds for 200 mL and 38 seconds for 500 mL) [65,66]. The intraesophageal and intragastric temperatures will be monitored using thermocouples, which is a widely used technique [67]. As currently there is no specific dynamic model for real-time monitoring or measuring of temperature changes of digested meals or drinks along the alimentary tract, inner food and drink temperature will be estimated using the inverse heat conduction problem methodology on surface temperature measurements obtained using thermography [68]. For practical and physiological purposes, considering the applied speed of ingestion, the magnitude of temperature changes along the alimentary tract could be considered as negligible [65-67,69,70].

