### Measures

All outcome measures will be measured at 0, 6, and 12 weeks. The participants will be asked to follow their assigned diet served at 37 °C, 42 °C, 47 °C, and 52 °C for 12 weeks.

Blood samples will be collected from each participant for analysis after 12-hour fasting, 3 times during the study (at the beginning and 6 and 12 weeks later).

Adipose tissue biopsies, protein isolation, and in vitro cell culture experiments will be performed as described elsewhere [33].

Cellular HSP-70 and HSP-90 levels will be measured to determine the thermic response to feeding, that is, evaluation of the causal relationship among higher dietary temperature, HSP-70/HSP-90 concentrations, and their time profile, as well as measures of obesity, aerobic fitness, resting metabolic rate, and diet-induced thermogenesis.

Food diaries will be analyzed using software to determine energy intake and macronutrient content.

An automated respirometer system plus a whole-body direct calorimeter, as the gold standard, will be used to measure energy expenditure and substrate utilization, aerobic fitness, resting metabolic rate, diet-induced thermogenesis, and markers of protein and fat catabolism to evaluate whether dietary temperature influences metabolism and surrogate end points of obesity in participants, such as weight and waist-hip ratio.

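### Resting metabolic rate and diet-induced thermogenesis appear to be read in an unexplained 35 °C calorimeter, 10 °C above the plan's own thermoneutral reference and during habituation

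*Protocol article*

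**What the plan says.** In the protocol article, Procedures says that participants "will be instrumented in a thermoneutral room (approximately 25 °C" and are then moved to a "whole-body calorimeter regulated to 35 °C with approximately 20% relative humidity". There they sit for a "30-minute habituation period while steady-state measurements will be obtained". No other calorimeter setting is described, and no reason is given for 35 °C.

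Measures says that a respirometer together with a direct calorimeter will be "used to measure energy expenditure and substrate utilization, aerobic fitness, resting metabolic rate, diet-induced thermogenesis" and other markers. The purpose given is to learn whether dietary temperature influences metabolism and surrogate endpoints of obesity.

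The background sections treat ambient temperature as active. Thermic Response lists, among the influences on the thermic response, "multiple environmental factors (such as gas concentration and ambient temperature". Weight Regain and HSPs states: "Exposure to low or high ambient temperatures directly impacts heat production and energy balance in pigs".

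**The concern.** The trial asks whether heat delivered in food changes energy metabolism. Its calorimetry adds a second source of heat, in the same session and without explanation, and the plan's own background says that ambient temperature alters the thermic response. A value read at 35 °C is not a resting metabolic rate in the condition that the plan calls thermoneutral.

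Timing adds to this. Steady state is assumed during the habituation itself, straight after a 10 °C step. Direct calorimetry records heat loss, which equals heat production only while body heat storage is stable.

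What is at stake is interpretation. If the arms do not differ on these measures, it would be harder to tell whether meal temperature has no effect or whether the conditions of measurement blurred a small one.

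**Working it through.** The plan gives no expected effect or standard deviation for resting metabolic rate or diet-induced thermogenesis, so there is no stated figure to reproduce. The checks below only set the scale.

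**Inputs from the protocol article**
- Room about 25 °C and chamber 35 °C (Procedures). Step: 35 − 25 = 10 °C.
- Measurement window: the 30-minute habituation (Procedures).
- "boluses of soups (each 100 ml) with a predefined temperature" (Procedures).
- Arms at 37, 42, 47 and 52 °C (Measures), so the largest contrast is 52 − 37 = 15 °C. Sample Size Calculation gives 49 and 54 °C for the two hottest arms. The two sections must be reconciled, but the choice does not change the conclusion here.
- 20 participants per arm (Sample Size Calculation).

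**Assumptions, not in the documents**
- Soup has the specific heat of water, 4.186 kJ/kg/°C.
- Dry heat-transfer coefficient 4 to 8 W/m²/°C, body surface 1.9 to 2.2 m², skin temperature held fixed.
- Body mass 85 kg, tissue specific heat 3.5 kJ/kg/°C.
- Daily intake 2000 to 2500 kcal from soup of 0.5 to 1 kcal/mL.
- Two-sided alpha 0.05, normal approximation, no adjustment for multiplicity.

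**1. Extra heat in one bolus relative to 37 °C** = mass × specific heat × temperature difference.
- 42 °C: 0.1 × 4.186 × 5 = 2.1 kJ
- 47 °C: 0.1 × 4.186 × 10 = 4.2 kJ
- 52 °C: 0.1 × 4.186 × 15 = 6.3 kJ (about 1.5 kcal)
- 54 °C: 0.1 × 4.186 × 17 = 7.1 kJ

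**2. Extra heat over a day at +15 °C.** Volume = intake ÷ energy density, at about 1 kcal per litre per °C.
- Smallest: 2000 kcal at 1 kcal/mL is 2 L, giving 2 × 15 = 30 kcal, or 1.5% of intake.
- Largest: 2500 kcal at 0.5 kcal/mL is 5 L, giving 5 × 15 = 75 kcal, or 3% of intake.

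**3. Change in dry heat exchange from 25 to 35 °C** = coefficient × area × 10 °C.
- Low: 4 × 1.9 × 10 = 76 W; over 1800 s, 137 kJ.
- High: 8 × 2.2 × 10 = 176 W; over 1800 s, 317 kJ.
- Relative to one 52 °C bolus: 137 ÷ 6.28 ≈ 22, and 317 ÷ 6.28 ≈ 50.

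**4. Heat storage if steady state is not reached** = mass × specific heat × drift. A drift of 0.1 °C in mean body temperature stores 85 × 3.5 × 0.1 ≈ 30 kJ, nearly five times the extra heat of one 52 °C bolus (30 ÷ 6.3 ≈ 4.8).

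**5. What this means between arms.** The shift in step 3 is common to all arms and cancels in the expected difference. Information is lost only if 35 °C raises the between-person standard deviation or shrinks the response. For illustration, with 20 per arm and an assumed pairwise standardised effect of 0.9 (raw effect unchanged):

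| SD multiplied by | Power |
|---|---|
| 1 | 0.81 |
| 1.25 | 0.62 |
| 1.5 | 0.48 |
| 2 | 0.30 |

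The documents give no basis for choosing a row.

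**The case against.** The strongest reply is that the chamber is the same for every arm, so randomisation protects the contrast. That stands. A reader might infer that the ambient load masks the meal-temperature effect, but the documents do not support this. Masking would need a larger variance or an interaction, and the plan gives no value for either. The energy totals in steps 1 to 3 do not prove it either: the hypothesis concerns induction of heat shock proteins, not simply the heat carried in the soup.

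Second, no single sentence says that resting metabolic rate is read at 35 °C. Measures names two instruments, gives no condition for the respirometer, and lists aerobic fitness in the same sentence, which seated rest cannot supply. This also stands. The reading is an inference from Procedures and Measures together, but a strong one, since only one calorimeter condition is described.

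Third, the plan calls the instrumentation room thermoneutral and never promises thermoneutral calorimetry. The sequence may be a chosen heated-chamber method, with its reason left to a fuller protocol. That is fair as to a strict contradiction. It does not settle the labelling: the stated set-point and the use of habituation as the measurement window conflict with calling the result resting.

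Two further inferences should be resisted:
- Weight Regain and HSPs cites an ambient range of 12 to 29 °C from animal work. The plan uses it to justify a temperature difference for diets, so it is not a limit that the chamber exceeds.
- The heat shock protein samples are not shown to be affected. Blood is drawn after a 12-hour fast, and its order relative to chamber entry is not stated.

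Last, these calorimetric measures are in none of the primary, secondary or other outcome lists, which limits the impact.

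**Conclusion.** The point holds as a problem of measurement condition and labelling. Procedures and Measures together imply that resting metabolic rate and diet-induced thermogenesis are read 10 °C above the plan's own thermoneutral reference, with steady state assumed during habituation and no reason given. The randomised comparison is not biased by this. Added variance or an attenuated contrast is plausible, given the small heat signal (30 to 75 kcal a day at +15 °C under the stated assumptions) and the much larger ambient shift, but its size cannot be derived from the documents.

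Severity is minor to moderate. The measures are outside the listed outcomes, yet Measures uses them to address whether dietary temperature affects metabolism. The conclusion depends on reading the two sections together. It does not depend on the assumed heat-transfer, body-mass or power figures.

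**What to change.** - Take resting and post-meal calorimetry at the condition that the plan itself calls thermoneutral (about 25 °C).
- Start measurement after habituation, not during it, and state how steady state is judged.
- State the ambient condition for each calorimetric and respirometric measure.
- Draw the fasting blood for heat shock proteins before chamber entry, and say so.
- If 35 °C is deliberate, give the reason and report the outcome as energy expenditure under heat load, not as resting metabolic rate.

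The cost is a chamber set-point, a somewhat longer session and a few sentences; Results says that the trial has not been initiated. The downside of moving to the thermoneutral condition is less comparability with heated-chamber methods.
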